### Outcome measures

2.10

#### Primary outcome

2.10.1

Total clinical effective rate

Overall clinical effectiveness will be assessed at 2 time points: at week 4 and during the follow-up period (month 1). These specific time points are chosen to evaluate the immediate therapeutic effects following the completion of the 4-week treatment course and to determine the short-term sustainability of these effects 1 month after the intervention has ceased. It will be classified into the following 3 grades according to the Guidelines for Clinical Study of New Chinese Medicines:

Cure: clinical symptoms such as limb numbness, coldness and chilling pain, sensory abnormalities, muscle weakness, and muscle atrophy disappear, tendon reflexes return to normal, and the total score of TCSS is ≤ 5 points;Effective: numbness of the limbs, cold and chilling pain, sensory abnormalities, muscle weakness myasthenia, and other clinical symptoms significantly improved, tendon reflexes returned to normal, TCSS score level 2 or 1 level lower;Ineffective: clinical symptoms did not improve or worsen, tendon reflexes were not elicited, and TCSS score grade did not decrease or increase.

Total effective rate = [(number of cured cases + number of effective cases)/total number of cases] × 100%.

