Acupuncture therapy is a traditional Chinese medical practice that entails the insertion of needles into certain points on the body to stimulate and treat various diseases (9–11). From an evidence-based perspective, acupuncture can modulate the nervous system and other physiological processes to produce theraputic effects like pain relief (12–15). A meta-analysis reveals that acupuncture, when combined with conventional treatment, successfully alleviates discomfort associated with DPN (16). Our early research concentrated on the fundamentals of acupuncture analgesia (17, 18), as well as a clinical study on the difference in moxibustion-induced microcirculatory responses in different meridians (19). In terms of clinical practice, moxibustion is similar to acupuncture, can treat DPN, considerably improve patients’ symptoms, and has few side effects (16, 20). Moxibustion is a supplementary and alternative therapy in which mugwort is burned at certain acupoints to offer warming stimulation for treatment and recovery (21, 22). From an evidence-based viewpoint, moxibustion potentially exerts effects through thermal stimulation that may influence local circulation and neural pathways (23–25). Moxibustion on appropriate acupoints in DPN patients can successfully improve local neurotrophic symptoms, improve nerve cell function, boost sensitivity and nerve conduction velocity, and have significant therapeutic effects (19, 26).

Emerging clinical evidence suggests that moxibustion can alleviate DPN-associated pain and numbness (20). However, its therapeutic protocols remain unstandardized, particularly with respect to treatment duration. Existing studies report a wide range of moxibustion durations—from a few minutes to as long as 30 min—with little consensus on the optimal timeframe or its impact on efficacy. This gap in knowledge hinders the broader adoption and optimization of moxibustion as a viable treatment for DPN.

Therefore, we hypothesize that the combination of moxibustion and conventional treatment for diabetic peripheral neuropathy is more efficacious than conventional treatment alone. Nonetheless, the distinction in efficacy between the 15-min moxibustion group and the 30-min moxibustion group necessitates further investigation.

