#### Statistical analysis

2.10.3

Statistical analysis of the data will be performed by a third-party statistician who will not involved in the pre-test, using the statistical software IBM SPSS Statistics version number (SPSS 26.0). Measurement information to meet the normal distribution of the use of the mean ± standard deviation table, counting information is expressed in the number of cases (%). The non-parametric rank sum test was employed for group comparisons, while chi-square analysis will facilitate additional group comparisons. Furthermore, a mixed linear model, COX regression analysis, and logistic regression analysis will be utilized for the exploratory examination of factors influencing the primary outcome indices. For missing data handling, multiple imputation will be employed for primary outcome analyses. A *p*-value of less than 0.05 indicates that the differences are statistically significant. Statistical analyses will be conducted by qualified statisticians. Upon completion of data entry and review, statisticians must finalize the statistical analysis promptly and produce a written report detailing the findings.

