#### Sample size estimation

2.10.4

The sample size was calculated based on the primary outcome, defined as the clinical effectiveness rate. Drawing from prior studies and pilot data, the effectiveness rate for the conventional treatment group was estimated at 60%, while the moxibustion groups were hypothesized to achieve an effectiveness rate of 90%. A two-sided test was adopted with a significance level (*α*) of 0.05 and a statistical power (1-*β*) of 90%, ensuring adequate sensitivity to detect the specified effect size, the calculation yielded a minimum of approximately 24 participants per group. To accommodate an anticipated dropout rate of 20%, the sample size was adjusted upward to 30 participants per group. With three study groups, this results in a total sample size of 90 participants.

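### The primary outcome has two unranked time points and three arms under one flat p<0.05 rule, so the false-positive rate for the primary conclusion exceeds 5%: about 8–10% to 19–24%, depending on how the tests are read

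*Protocol article*

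**What the plan says.** - **Time points** (Primary outcome, 2.10.1): "Overall clinical effectiveness will be assessed at 2 time points: at week 4 and during the follow-up period (month 1"). Week 4 is there to show the immediate effect and month 1 to show whether it lasts. Table 1 ticks both visits for this outcome. Neither is designated primary.
- **Hypothesis** (Introduction): "the combination of moxibustion and conventional treatment for diabetic peripheral neuropathy is more efficacious than conventional treatment alone". The same paragraph says that the difference between 15 and 30 min needs further study.
- **Aim** (end of the Introduction, and Conclusion): to compare 15 with 30 min and identify the best duration.
- **Test and decision rule** (Statistical analysis, 2.10.3): chi-square is named for comparing groups, without saying whether it is three-group or pairwise. A p-value "of less than 0.05 indicates that the differences are statistically significant". No order of testing and no adjustment is given.
- **Sizing** (Sample size estimation, 2.10.4): "the effectiveness rate for the conventional treatment group was estimated at 60"%, and "the moxibustion groups were hypothesized to achieve an effectiveness rate of 90"%, at two-sided 0.05 with 90% power. This is one rate difference, with the same rate assumed for both moxibustion arms.

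**The concern.** A 5% significance level describes one test. Here the primary outcome is looked at on two visits and in three arms, and any difference with p below 0.05 counts as significant. Several results could each be reported as a positive primary finding, so the chance that at least one is false is larger than 5%.

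The trial exists to recommend a duration for standardised care. As written, a chance result for one duration at one visit could be presented as that recommendation, and nothing in the text would mark it as one of several attempts.

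**Working it through.** **Inputs from the article.** Three arms at 1:1:1; 24 evaluable or 30 randomised per arm; two visits; 0.05 per test; conventional rate 60%, moxibustion rate 90%.

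**Assumption, not in the article.** The within-patient correlation between week 4 and month 1, taken as phi about 0.3–0.7 (latent normal correlation 0.5–0.9). The success rate common to all arms under the null is taken as 60% or 75%.

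**The plan's own figure.** The article states no familywise error rate, so there is none to reproduce. Its related figure is 24 per group. The usual pooled formula for one comparison is

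n = [z(0.975)·√(2p̄q̄) + z(0.90)·√(p₁q₁ + p₂q₂)]² / Δ²

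With p̄ = 0.75 and Δ = 0.30 this is [1.960 × √0.375 + 1.282 × √0.33]² / 0.09 = 1.9365² / 0.09 ≈ 41.7, so 42 per arm. The stated 24 does not follow from the stated inputs. That is a separate matter. What counts here is that the sizing covers one comparison at 0.05.

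**How many tests.** Pairwise contrasts: 15 min vs conventional, 30 min vs conventional, 15 vs 30 min. Over two visits that makes 3 × 2 = 6 tests, or 2 × 2 = 4 if only moxibustion vs conventional counts. A three-group test at each visit makes 2. Treating six tests as independent gives an upper reference of 1 − 0.95⁶ = 26.5%. The real tests are correlated, so simulation is needed.

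**Simulation.** Binary outcomes with equal rates in all arms, Pearson chi-square without continuity correction, 24 or 30 per arm. The result is the chance of at least one p < 0.05:

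| Reading of the plan | Tests | Chance of a false positive |
|---|---|---|
| Three-group chi-square at each visit | 2 | 8.4–9.7% |
| Moxibustion vs conventional, both arms, both visits | 4 | 14.3–18.3% |
| All pairwise tests, both visits | 6 | 18.7–24.0% |
| Three pairwise tests at one visit only | 3 | 11.8–13.4% |

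The last row shows that naming one visit is not enough if three ungated pairwise tests remain.

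**Sensitivity to the assumed correlation** (normal approximation, correlation 0 to 0.9): two three-group tests 9.8% to 7.1%, four tests 17.2% to 12.7%, six tests 22.9% to 16.7%. At a correlation of exactly 1 these become 5.0%, 9.1% and 12.3%.

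**Check of the remedy.** With three groups, any two true pairwise null hypotheses imply that all three rates are equal. A three-group test at 0.05 that gates pairwise tests at 0.05 is therefore a closed test procedure. Simulated familywise error under the global null at one visit: 4.9–5.0%. Under 60%/90%/90% the three-group test has power of about 75% at 24 per arm and 85% at 30.

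**Check of a fixed sequence.** The order is pooled moxibustion vs conventional, then 30 min vs conventional, then 15 min vs conventional, then 30 vs 15 min. Power of the first step is 0.85 (24 vs 48) to 0.92 (30 vs 60). All three gates ahead of the duration comparison pass in 57.6% of trials at 24 per arm and 68.9% at 30.

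**The case against.** The strongest defence is that this is a condensed article with no SAP at hand, that multiplicity is commonly settled in a SAP, and that p < 0.05 is only a general convention. This stands so far as the mere absence of a multiplicity paragraph goes, and that absence is not held against the document. But the article does fix things. It puts two visits under the primary outcome, states a flat threshold, and directs its hypothesis and its aim at different contrasts. A SAP that controlled the error would have to rank what the article leaves unranked.

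Three stronger readings are tempting and not supported:

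- **That the error rate simply is 19–24%.** This needs six pairwise tests, all primary, with no three-group test first. The Statistical analysis section allows that but does not state it, and a three-group chi-square at each visit fits the text equally well. The figure also depends on a correlation the article does not give.
- **That there is no primary contrast at all.** The hypothesis and the sample size both point to moxibustion against conventional treatment. That still leaves two arms and two visits.
- **That the two visits are interchangeable.** The article gives them different purposes, and lasting effect presupposes an immediate one. But this is not a stated order of testing.

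**Conclusion.** The point holds in a reading-dependent form. Followed as written, the plan does not hold 5% for the primary conclusion: about 8–10%, 14–18%, or up to about 19–24% under the three readings of the two-visit plan. These ranges assume phi of about 0.3–0.7, equal true rates of 60–75%, and 24–30 patients per arm. The direction does not depend on those choices. Only perfect correlation between visits combined with the three-group reading brings the rate down to 5%.

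**What to change.** - Name week 4 as the single primary time point. Make month 1 secondary, as the measure of sustainability.
- At week 4, do a three-group chi-square at two-sided 0.05. Only if it is significant, do the three pairwise tests, each at 0.05. State that this order controls the familywise error because there are exactly three groups.
- Record this before any outcome data are seen.

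The change takes a few sentences and no extra patients. The price is that if the overall week-4 test fails, no pairwise and no month-1 result can be claimed as a primary finding. At the article's own rates the overall test fails in about 25% of trials at 24 per arm and 15% at 30.

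A fixed sequence starting with pooled moxibustion against conventional treatment is an alternative with a stronger first step. With 30 vs 15 min placed last, however, the duration question is reached in only about 58–69% of trials at the assumed 60% and 90%. That suits a trial whose stated aim is duration less well.

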#### Secondary outcomes

2.10.2

Electrophysiological examination

The electrophysiological examination will be detected at week 0 and after 4 weeks of treatment (week 4). The latency, amplitude, motor nerve conduction velocity (MNCV), and sensory nerve conduction velocity (SNCV) of the tibial nerve and peroneal nerve of the lower extremities will be measured before and after treatment.

Toronto Clinical Scoring System (TCSS)

The TCSS is a valid instrument to reflect the presence and severity of diabetic peripheral sensorimotor polyneuropathy as measured by sural nerve morphology and electrophysiology (29). TCSS will be estimated at week 0, week 4, and month 1.

Visual Analogue Scale (VAS)

The level of pain at the subject’s lesion site will be determined using the VAS scale, which classifies pain on a scale of 0–10, with the greater the number the more pronounced the pain, i.e., a score of 0 indicates no pain, 1–3 represents mild pain, 4–6 represents moderate pain, 7–9 represents severe pain, and 10 represents severe pain. Participants will be allowed to indicate the level of pain by crossing out specific numbers on the scale according to their actual situation. The VAS scale will be administered at week 0, week 4, and month 1.

Traditional Chinese Medicine Syndrome Score Scale (TCMS)

The evaluation of the curative effect of TCMS should refer to the guiding principles of clinical research of new drugs of traditional Chinese medicine and the clinical evidence-based practice guide of traditional Chinese medicine for diabetes. TCMS will be estimated at week 0, week 4, and month 1.

The specific records are as follows:

The VAS score of limb pain was consistent according to the severity.The three main traditional Chinese medicine syndromes of limb numbness, abnormal chill (or fever), and ant feeling were scored as 0, 1, 2, and 3 points, respectively, according to their severity.

Infrared thermography

The test sites will be bilateral plantar, dorsal, palmar, and dorsal hands. The instrument used is the NECR450 infrared thermal imager produced by NECAVIO Company in Japan. Infrared thermography testing will be performed once at week 0 and once at week 4.

#### Statistical analysis

2.10.3

Statistical analysis of the data will be performed by a third-party statistician who will not involved in the pre-test, using the statistical software IBM SPSS Statistics version number (SPSS 26.0). Measurement information to meet the normal distribution of the use of the mean ± standard deviation table, counting information is expressed in the number of cases (%). The non-parametric rank sum test was employed for group comparisons, while chi-square analysis will facilitate additional group comparisons. Furthermore, a mixed linear model, COX regression analysis, and logistic regression analysis will be utilized for the exploratory examination of factors influencing the primary outcome indices. For missing data handling, multiple imputation will be employed for primary outcome analyses. A *p*-value of less than 0.05 indicates that the differences are statistically significant. Statistical analyses will be conducted by qualified statisticians. Upon completion of data entry and review, statisticians must finalize the statistical analysis promptly and produce a written report detailing the findings.

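### Cox regression and a linear mixed model are named only for exploring a binary outcome read at two fixed visits, and no baseline-adjusted method is named for the continuous secondary outcomes

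*Protocol article*

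**What the plan says.** All the methods are in the Statistical analysis section (2.10.3) of the protocol article.

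- Group comparisons: "The non-parametric rank sum test was employed for group comparisons, while chi-square analysis will facilitate additional group comparisons". Neither test is tied to a named outcome, visit or quantity (raw value or change).
- Models: "a mixed linear model, COX regression analysis, and logistic regression analysis will be utilized for the exploratory examination of factors influencing the primary outcome indices". No other use is given for any of the three.

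The Primary outcome section (2.10.1) grades each patient as cured, effective or ineffective and reduces this to a proportion: "Total effective rate = [(number of cured cases + number of effective cases)/total number of cases] × 100" per cent. It is read at week 4 and at the one-month follow-up. No event time, time origin or censoring rule is given.

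The Secondary outcomes section (2.10.2) and Table 1 schedule a baseline value for every secondary measure. TCSS, VAS and TCMS have two later readings: "TCSS will be estimated at week 0, week 4, and month 1", with the same timing for VAS and TCMS. Electrophysiology and infrared thermography have one later reading, at week 4.

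**The concern.** Two things look wrong, and they are not equally firm.

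The firm part is stated in the text. Two of the three models are tied to an outcome they do not fit. Cox regression models time to an event. Here there is only a status at two scheduled visits, and that status can reverse, since the month-1 visit is there to see whether the effect lasts. A hazard ratio from such data would mainly reflect the visit calendar. A linear mixed model assumes a continuous response with roughly constant variance, which a yes/no outcome does not have.

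The second part is an inference. With every model reserved for the primary outcome indices, TCSS, VAS, TCMS, nerve conduction and skin temperature are left with a rank-sum test. As named, that test does not use the baseline value. It also gives no adjusted difference with a confidence interval. What is at stake is precision in a trial of 24 to 30 patients per arm, including for the 15-min versus 30-min contrast that motivates the study.

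**Working it through.** **1. Match each named method to the outcomes.** The plan gives no figure on this point to reproduce, so the first step sets the sections side by side.

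| Outcome | Type and timing in the protocol | Method the text supports | Fit |
|---|---|---|---|
| Effective rate (primary) | Binary, week 4 and month 1 | Chi-square (group comparison; inferred) | Suitable |
| | | Logistic (exploratory) | Suitable |
| | | Linear mixed model (exploratory) | Does not suit a binary response |
| | | Cox (exploratory) | No event time |
| TCSS, VAS, TCMS | Scores at week 0, week 4, month 1 | Rank-sum (by elimination) | Valid, inefficient |
| Electrophysiology, thermography | Continuous, week 0 and week 4 | Rank-sum (by elimination) | Valid, inefficient |

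The elimination: chi-square does not suit measured scores, velocities or temperatures, and the models are reserved. Only the rank-sum test remains.

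**2. Size of the efficiency loss.** The baseline-to-follow-up correlation *r* is not in the documents. It is assumed here to be 0.3, 0.5 or 0.7, with equal variances at both times. Relative to a comparison of raw follow-up values:

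- ANCOVA variance factor = 1 − r²: 0.91, 0.75, 0.51, a saving of 9%, 25%, 49%.
- The rank-sum test has efficiency 0.955 for normal data. Relative to ANCOVA its efficiency is 0.955 × (1 − r²): 0.87, 0.72, 0.49.
- Change-score variance factor = 2(1 − r): 1.4, 1.0, 0.6. Change scores are therefore worse than raw values at r = 0.3, equal at 0.5 and better at 0.7.

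**3. The same in power terms (illustration).** Assume a standardised difference d = 0.6 and two-sided α = 0.05, with 30 per arm from the Sample size estimation section. By the normal approximation, power = Φ(d√(n/2) × √(efficiency ÷ variance factor) − 1.96), and d√(n/2) = 0.6 × √15 = 2.324.

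- Rank-sum, raw week-4 values: Φ(2.27 − 1.96) = 0.62.
- ANCOVA, r = 0.5: Φ(2.68 − 1.96) = 0.77 (0.765 before rounding the terms).
- ANCOVA, r = 0.7: Φ(3.25 − 1.96) = 0.90.
- Rank-sum on change scores, r = 0.7: Φ(2.93 − 1.96) = 0.83.

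At r = 0.7 the gain is therefore 62% to 90% if the test is run on raw values, but 83% to 90% if it is run on change scores.

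**4. How large a logistic model the primary outcome can carry.** At the planned rates of 60%, 90% and 90% with 30 per arm, expected ineffective cases = 30 × (0.4 + 0.1 + 0.1) = 12 + 3 + 3 = 18. A model with arm (2 parameters), baseline TCSS (1) and centre (2) has five slopes: 18 ÷ 5 = 3.6 ineffective cases per parameter. At 24 per arm, 24 × 0.6 = 14.4 cases and 14.4 ÷ 5 = 2.9 per parameter. That is sparse, so few covariates can be entered.

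**The case against.** The strongest reply is that the rank-sum sentence attaches the test to nothing. It could be meant for the three ordered grades of effectiveness, where it fits well, or be run on change from baseline. A condensed article may leave the mapping of tests to outcomes, covariates and confidence intervals to a full protocol or SAP that is not shown. A rank-sum test on bounded scales is valid, and preferring an adjusted model is a matter of efficiency. This stands. A reader might infer that the protocol assigns an unadjusted rank-sum test to the repeated scales, or that the methods have been swapped between outcomes. The text does not say so; it only leaves no other named method for those scales.

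A second reply is that the three models are labelled exploratory. This also stands. A reader might infer that the confirmatory primary comparison rests on Cox regression or a linear model. Nothing in the documents supports that: chi-square is named and suits a comparison of rates.

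A third reply is that the plural, primary outcome indices, might include the TCSS score, which feeds the effectiveness grades and would suit a linear mixed model. That is possible, but the protocol lists TCSS as secondary, and the reading would not rescue Cox regression.

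Finally, the power figures depend on an assumed d and r, and the larger gap also on raw week-4 values. They illustrate the gain; they are not estimates for this trial.

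**Conclusion.** The point holds in two parts of different strength. Firmly: Cox regression is wrong as written for an outcome with no event time, and a linear mixed model does not suit a binary rate. An SAP would have to contradict the sentence, not merely fill it in. The harm is confined to the exploratory analysis.

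By inference: no baseline-adjusted method is named for any continuous secondary outcome, although baseline is scheduled for all of them. The remaining test is valid but inefficient. The variance saving from adjustment, against raw follow-up values, is 9% to 49% for assumed correlations of 0.3 to 0.7. Against change scores it is the same 25% at r = 0.5 and smaller above that. None of this affects the trial's sizing, which is on the binary rate. It is worth correcting because the improvement is concrete and nearly free.

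**What to change.** Rewrite the Statistical analysis section so that each outcome has a named method.

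- **Primary comparison:** keep chi-square for the effective rate.
- **Exploratory factor analysis:** keep logistic regression, at one named visit and with few covariates given about 18 expected non-responders. Delete Cox regression, and do not apply the linear mixed model to the binary rate.
- **TCSS, VAS, TCMS:** linear mixed model with baseline value, arm, visit and arm-by-visit.
- **Electrophysiology and thermography:** ANCOVA on the week-4 value, adjusted for baseline.
- **Reporting:** adjusted differences with 95% confidence intervals, with the rank-sum test kept as a sensitivity analysis for skewed or bounded scores.

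The cost is a change of wording. The baseline values are already scheduled, and the named software fits these models. The downside is a modest reliance on modelling assumptions for bounded scales such as VAS and TCMS, which the rank-sum sensitivity analysis covers.
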